## **5.7 Fitbit Data**

Data collected through Fitbits will include physical activity and sleep data.

# **6. Specimen Procedures/evaluations**

## **6.1 Specimen preparation, handling, and storage**

Venous blood for research purposes (not for standard clinical lab testing) will be collected by the Duke Clinical Laboratory in research tubes. All samples will be labeled with a unique RESILIENCE Study ID and barcoded. No personal health information will be used to label, track, or identify specimens. These tubes will be hand-collected by the CRC after the blood draw, and will be centrifuged, aliquoted, labelled, and stored in a -20°C freezer at the Duke South Durham Clinic. At regular intervals, these aliquots will be

transferred to the Duke Molecular Physiology Institute (DMPI). The saliva and stool specimen samples will be mailed back by individual patients directly to the DMPI.

Once received, the venous blood, saliva and stool specimens collected under this protocol will be stored in a dedicated portion of the Duke Molecular Physiology Institute (DMPI), in locked -80°C and liquid nitrogen (LN2) freezers. Newly collected blood and stool specimens will be processed, analyzed and stored in [name] (DMPI) laboratory at the Carmichael Building, [name]. All samples will be labeled with thermo-safe uniquely barcoded Acquisition numbers, will be scanned into a spreadsheet freezer location template upon arrival to [name] laboratory, and will be tracked throughout the life of the sample. Specimens collected are logged in a secure, encoded database.

## **6.2 Biobanking of samples**

All samples will be banked for future research use. We will offer all participants the opportunity to participate in a biorepository for blood and stool storage. This biorepository sub-study aims to store subjects' plasma, DNA, and fecal samples long-term for future research. The two studies are identical in terms of sample collection. Subjects may consent for either study, both studies, or neither study and can choose to opt in or out for participation in the bio-repository. If subjects consent for both studies, an aliquot of the biorepository samples will be used for the observational trial; therefore the volume of blood and stool collected is the same if a subject consents for one study or both studies. Maximum blood drawn per participant will not exceed 85mL over any eight-week period.

DMPI will be used for long-term sample storage and sample routing. Biospecimens sent to the central biospecimen storage facility for banking will remain there until withdrawn for protocol-specified testing, unspecified future research, or until exhausted. Samples for storage for future use will be logged into the biobanking storage system using a unique identifier so their location may be tracked within the storage facility.

Please see full biorepository protocol for details which will be submitted to the IRB as a separate new study application (Pro00106060).

## **7. Participant Retention and Withdrawal**

### **7.1 Strategies for Retention**

Over the course of the study, a diverse set of approaches for participant engagement and retention may be employed, including but not limited to:

- Follow-up calls from a member of the study team
- Video, live-stream, or in-person engagement events
- Newsletters with opportunities to be featured or contribute content
- Feedback surveys so participants can voice their opinions
- Personalized thank you notes
- First access to research publications and other study updates
- Social media platforms such as Twitter, Facebook, YouTube, and Instagram

### **7.2 Discontinuation of Participants**

#### **7.2.1 Non-Compliance**

At the start of the study, if participants do not return ALL THREE of their biospecimens, they will not be able to continue in the remainder of the study. During the study, participants may miss an onsite visit, not respond to a survey, not respond to the TRACK intervention or health coaches, or stop using the devices.

All efforts to regain contact will be documented and retained with the participant records. A documented effort may include multiple forms of communication. This may include, but is not limited to, the Investigator, his/her delegate, or other study personnel attempting to regain contact via the Mytonomy platform, email, mail, phone, or text.

### **7.2.2 Stopping study procedures or withdrawal**

Participation in this study is voluntary and participants may withdraw at any time. In the event the participant chooses to withdraw, he/she will be instructed to contact the study team immediately. If a participant decides not to participate, or if they choose to drop out after the study has started, he/she may withdraw at any time without jeopardy or penalty.

During the study, participants may decide that they would like to stop some or all of the study visits or follow-up. In the event a participant requests to stop his/her involvement in the study, the participant may immediately stop all activities but will also be given several other options. These may include but are not limited to completing all or some of the in-person visits and/or active follow-up (e.g., telephone calls, email contact only) and/or passive follow-up (e.g., contact with care providers, review of health records). If a participant expresses interest in withdrawing from the study, the study team will contact the participant and give him/her options to reduce their level of participation. This includes, but is not limited to, opting out of certain study activities. After discussions with the study team, including the Investigator or his/her delegate, if the participant decides to stop all participation in the RESILIENCE Study and withdraw entirely, the study team will inform the participant of the withdrawal process. This includes requesting information from the participant such as feedback about participation or withdrawal from the study. Participants may be asked to provide written confirmation of withdrawal. Once this information is received, further attempts to contact the participant or collect additional information will not be undertaken unless it is necessary for device retrieval. Information that has already been gathered may still be used. Participants may withdraw from the study at any time without prejudice to their care. This will not preclude the participant from re-establishing contact with the study in the future. In the event of a participant withdrawing, the RESILIENCE Team will make every effort to help the participant return all investigational devices in their possession.

### **7.2.3 Replacement**

Participants who do not return their initial biospecimens will not continue in the study, and they will be replaced. Participants who withdraw from the study once enrolled (and after returning the three biospecimens) will not be replaced.

### **7.2.4 Exiting Participants**

Participants will be exited from the study for the following reasons:

- Participant becomes pregnant
- Withdrawal of consent to participate in all visits and all forms of follow-up
- Death

Participants may be exited from the study for the following reasons:

- If a participant is uncooperative or noncompliant with respect to the provisions of the protocol
- To protect the participant for safety or for administrative reasons
- Investigator determines it is in the best interest of the participant
- If a participant does not consent to continue participating in the study after being told of changes in the research that may affect him/her
- If a participant engages in misconduct, or disassembles any device used in this study

## **8. Analytic Considerations**

### **8.1 Recruitment Sub-study**

We will compare recruitment strategies – email vs. my chart message and ego-centric vs. altruistic messaging – and randomize in a 2x2 fashion. We will make quarterly assessments to compare the four modalities. We will compare response rates between modalities using a binomial test. If it is determined that one modality is better than another, we will drop the weaker modality. The responses will further be analyzed within defined strata. We will use an alpha spending strategy  $p < 0.01$  allowing for a total of 5 comparisons for a total family wise error rate of 0.05.

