### **2.2. Secondary Aims & Hypotheses**

Aim 3: Optimal Recruitment Strategies. We aim to determine optimal strategies to recruit patients into the study remotely, i.e. without requiring a formal clinic visit or the direct involvement of the patient's clinician. Specifically, we want to understand whether an initial message through personal email vs. MyChart message leads to greater engagement, and whether the content of the message affects engagement. We will do this by randomizing potentially eligible patients in a 2x2 factorial fashion to personal email vs. MyChart message, and to different message content.

Hypothesis 3a: An introductory message delivered through MyChart will lead to greater engagement (as assessed by clicking on the study website page to get more information) than will a message delivered through personal email.

Hypothesis 3b: For patients with obesity, a message conveying altruism will lead to greater engagement than a message conveying personal benefit.

Hypothesis 3c: For patients without obesity, a message conveying altruism will lead to greater engagement than a message conveying scientific importance.

**Aim 4: Optimal Consenting Strategies.** We aim to determine optimal strategies to consent patients into the study remotely, i.e. without requiring a formal clinic visit or the direct involvement of the patient's clinician. Specifically, we want to understand which of the following formats leads to greater completion of the consent form and greater participant comprehension of the consent form: text only vs. text + physician video vs. text + patient video vs. text + animated video.

**Hypothesis 4a:** An informed consent form that includes both text and an animated video will lead to greater completion of the consent form and greater comprehension of the consent form compared with a text only, physician video, or patient video consent form.

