| Every day millions of people in the US struggle with their weight. Some respond to weight loss treatments while others do not. Likewise, some develop heart disease while others do not. We are doing the RESILIENCE study to understand more about these differences so that we can develop better treatments. | The RESILIENCE study aims to help people who want to lose weight and improve their heart health. We want to understand why some people with weight issues develop heart disease while others do not. Likewise, we want to understand why some people respond to weight loss treatments while others do not. | Millions of people in the US are at risk for heart disease, and weight is an important part of this risk. We are doing the RESILIENCE Study to understand the differences in heart health between people who have obesity and those who do not. | We know that weight is an important part of heart health. However, you may be surprised to know that we do not yet fully understand how weight affects heart health.                                                                                     |
| You may be a good fit for this study. Please think about joining Duke researchers in a study that will lead to better treatments for millions of                                                                                                                                                                | Participating in this study may make it possible for you to get better weight management and heart health treatments in the future. Please consider joining us in the RESILIENCE study!                                                                                                                     | Although you are not overweight, by joining this study you can help us understand these differences.                                                                                                                                            | We are doing the RESILIENCE study to understand why some people with obesity develop heart disease while others do not. Although you are not overweight, by joining the study, you can help us discover an answer to this important scientific question. |

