#### **4.1.1.3 Assessment of engagement**

All individuals will be randomized upfront as MyChart vs. e-mail invites. Obese group message will further be randomized as altruistic vs. personal benefit and non-obese group as altruistic vs. science focused. They all will also be provided with a unique ‘tracking’ URL which in turn will utilize application of FHIR ID (a unique identifying number that links specific participant information to Mytonomy). In order to determine the comparative effectiveness of the message content, data will be collected on the number of people who click on the ‘I’m interested’ button and subsequently arrive at the ‘landing’ page for further information. The arrival at the ‘landing’ page (which contains further information about the trial and further links to the eConsent portal) will be tracked using the original URL and embedded FHIR ID which after decryption will allow association back to identifying them as Duke patient with their first and last name, email address and mobile phone number. This will facilitate not only an understanding of which method is overall most successful in engaging patients (in aggregate) but also allow us to understand what type of approach is more likely to recruit certain types of patients (e.g. age, sex, ethnicity, geography etc.).

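### Protocol Section 8.1 plans one ego-centric vs. altruistic message comparison, but obese and lean patients get different comparators, so it either pools two contrasts or leaves Hypothesis 3c untested

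*Combined protocol and SAP*

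**What the plan says.** Protocol Section 8.1 describes the recruitment sub-study as a 2x2 comparison of "email vs. my chart message and ego-centric vs. altruistic messaging". On timing it says "We will make quarterly assessments to compare the four modalities", and on the test, "We will compare response rates between modalities using a binomial test". The decision rule is "If it is determined that one modality is better than another, we will drop the weaker modality". After that comes one sentence on strata: "The responses will further be analyzed within defined strata". Each comparison is made at p < 0.01, with five comparisons allowed for a family-wise error rate of 0.05.

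The randomisation is described differently. Protocol Section 4.1.1.3 says "Obese group message will further be randomized as altruistic vs. personal benefit and non-obese group as altruistic vs. science focused". Table 1 in Section 4.1.1.2 agrees: the lean group has an altruistic and a science-centric text and no personal-benefit text. Section 2.2 has a separate hypothesis for each group. Hypothesis 3b sets altruism against personal benefit in obese patients, and Hypothesis 3c reads "For patients without obesity, a message conveying altruism will lead to greater engagement than a message conveying scientific importance". Section 3.1 stratifies the randomisation by phenotype.

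**The concern.** Section 8.1 names one message contrast, while the trial runs two. The comparator differs by group, and Table 1 shows that even the altruistic text is worded differently for obese and lean patients. Four texts sent by two channels make eight cells, where Section 8.1 counts four modalities.

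Two things are at stake. The first is interpretation: a single message result would answer neither hypothesis, or would answer only 3b. The second is conduct: the drop rule names no stratum, so evidence coming mainly from the larger obese group could end a comparison in lean patients that their own data do not settle.

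**Working it through.** **The plan's own figure.** 5 × 0.01 = 0.05, so the stated family-wise rate reproduces. Section 8.1 gives no sample size, power or response rate for this sub-study. What follows is therefore about consequences and does not dispute a stated number.

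**Two readings of Section 8.1**

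| Reading | What is estimated | Hypothesis 3b | Hypothesis 3c |
|---|---|---|---|
| Pooled, with science-centric text counted as the non-altruistic arm | A weighted mix of two contrasts | Not estimated | Not estimated |
| Literal, ego-centric vs. altruistic | Obese contrast only | Tested | No planned test |

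**Inputs for the pooled reading**
- The obese share w of invited patients is not stated.
- Proxy from SAP Table 1: (541 + 454)/1,535 = 995/1,535 = 0.648. These people had already reached consent randomisation.
- Enrolment target (protocol Section 3.1): 400/600 = 0.667.
- Message differences d_obese and d_lean are assumptions; neither document gives any.

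**Dilution.** Pooled difference = w·d_obese + (1 − w)·d_lean.
- d_lean = 0: 0.648d, or 0.667d at the target mix.
- d_lean = −d: 0.648d − 0.352d = 0.30d, or 0.667d − 0.333d = 0.33d.

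**Cost in contacts when d_lean = 0** (similar response rates assumed across groups). The pooled test needs total contacts proportional to 1/(w·d)². An obese-only test needs obese contacts proportional to 1/d², hence total contacts proportional to 1/(w·d²). The ratio is 1/w: 1/0.648 = 1.54, or 1/0.667 = 1.5.

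**Sign.** With opposite effects, the pooled sign follows the obese stratum unless |d_lean|/|d_obese| exceeds w/(1 − w): 0.648/0.352 = 1.84, or 0.667/0.333 = 2.0.

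**Illustration of a wrong drop.** Assumed: 10% response to the comparator text in each stratum; altruistic text +3 points in obese and −3 points in lean patients; one look; two-sided 0.01; normal approximation; equal arms. At w = 2/3 the pooled difference is +1.0 point in favour of altruistic text, so a drop would remove the message that works better in lean patients.

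| Total invited (assumed) | Wrong drop in lean, w = 2/3 | Same, w = 0.648 | Lean-only test finds the right direction, w = 2/3 |
|---|---|---|---|
| 2,000 | 3% | 3% | 12% |
| 5,000 | 8% | 6% | 35% |
| 10,000 | 17% | 13% | 70% |
| 20,000 | 39% | 30% | 97% |

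Worked line, 20,000 invited and w = 2/3: 10,000 per arm, 11% vs. 10%. SE = √(0.11·0.89/10,000 + 0.10·0.90/10,000) = 0.00433; z = 0.01/0.00433 = 2.31; Φ(2.31 − 2.576) = 0.39.

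**The case against.** The strongest reply is that Section 8.1 never says obese and lean patients are pooled. The hypotheses, the message randomisation and the stratification are all specific to the group. Section 4.1.1.2 also uses egocentric as shorthand before pointing to a table split by group, and Section 8.1 may be doing the same. The strata it mentions are plausibly the four phenotypes defined elsewhere in the protocol. This stands as far as it goes: pooling is an inference. But a stratum-specific test is not written down either, and the strata sentence follows the test and drop rule as a further analysis. The SAP supplied covers Aim 4 only, so it does not settle the question.

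The harm is also conditional, and that stands too. Hypotheses 3b and 3c both predict that altruism wins. If it does, even a pooled rule drops the weaker text in each group. Dropping the better lean message requires effects in opposite directions; dilution requires only that the lean contrast be smaller.

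A reader might go further in three ways that the documents do not support.
- A 2.4-fold cost in contacts (1/0.648²). That compares the pooled test with a case in which lean patients also have effect d. Against the obese-only test that would replace it, the ratio is 1.54.
- A lean contrast that is bound to be small, because the science-centric text also appeals to helping: "by joining the study, you can help us discover an answer to this important scientific question". That is a judgement about wording, with no response data behind it.
- A decision made on a message that lean patients never saw. A pooled test would include their own responses; the trouble is that the obese responses would usually dominate.

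**Conclusion.** The point holds as a mismatch between Section 8.1 and the design it analyses. On the natural reading the message comparison estimates neither 3b nor 3c; on the literal reading 3c has no test. On either reading the drop rule is not confined to a stratum.

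Under pooling, a lean contrast of zero reduces the obese effect to about two-thirds and costs about 1.5 times the contacts of an obese-only test. With opposite effects, the obese stratum sets the sign unless the lean effect is about 1.8 to 2 times as large. These sizes rest on an obese share of 0.65 to 0.67. The first figure comes from people already selected on engagement, which is the Aim 3 outcome, and the second from an enrolment target. The lean effects, the response rate and the numbers invited are assumptions.

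A reader might infer that a message was wrongly dropped. The documents do not say whether any recruitment message was dropped, so that cannot be concluded.

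**What to change.** In Section 8.1, or in an analysis plan for Aim 3:
- Keep email vs. MyChart as one comparison, stratified by obese and lean.
- Replace the single message factor with two contrasts: altruistic vs. personal-benefit in obese patients (3b), and altruistic vs. science-centric in lean patients (3c).
- Apply the test, and any decision to drop a message, only within the stratum that supplied the evidence.
- Report no pooled message effect.
- Recount the comparisons and looks that share the 0.05. One channel and two message comparisons make three per look, so two looks already give six against the five allowed; an equal split over six would be 0.05/6 = 0.0083 each.

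SAP Section 2.3 puts the last invitations in March 2022, so the change now applies to analysis and reporting. The report should also state whether any message was dropped, in which stratum, and on what data.

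The cost is some wording and a stratified test, since randomisation was already stratified by phenotype. Each message contrast uses only its own stratum, so the lean comparison, with roughly a third of contacts on the proxy figures, is less precise than a pooled figure would be. The alpha per comparison may also have to be smaller than 0.01.

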#### 4.1.1 Electronic Recruitment: ‘eRecruitment’

Once identified as potentially eligible for the study, individuals will be assigned a recruitment/consent strategy based on block randomization of the 4 phenotypes (see Section 5.1). Two recruitment modalities and two recruitment messages will be tested in a 2x2 fashion (see Figure 1, below.).

**Figure 1.** 2 x 2 factorial randomization of method of contact and content of messages.

[figure not shown]

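### Section 8.1 does not define 'modality' or the test to use after a drop; if a single 2x2 cell is dropped, a pooled binomial test of a main effect is confounded by the other factor

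*Combined protocol and SAP*

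**What the plan says.** Section 8.1 of the protocol says the recruitment sub-study will "randomize in a 2x2 fashion", naming two contrasts: email against MyChart, and ego-centric against altruistic content. It continues: "We will make quarterly assessments to compare the four modalities". The test is given as: "We will compare response rates between modalities using a binomial test". The drop rule follows: "If it is determined that one modality is better than another, we will drop the weaker modality". The section then adds "The responses will further be analyzed within defined strata", without naming the strata. Each comparison uses p<0.01, "allowing for a total of 5 comparisons for a total family wise error rate of 0.05".

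Section 4.1.1 uses the key word differently: "Two recruitment modalities and two recruitment messages will be tested in a 2x2 fashion". There a modality is a contact method, listed apart from the messages.

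The hypotheses in section 2.2 are main effects. 3a compares MyChart with email. 3b reads: "For patients with obesity, a message conveying altruism will lead to greater engagement than a message conveying personal benefit". 3c is the matching message contrast for patients without obesity. The SAP in the file covers Aim 4 (consent) only.

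**The concern.** A 2x2 design gives a fair test of each factor because the other factor is balanced across its levels. Dropping one cell removes that balance for later invitees. If the email/ego-centric cell goes, every later ego-centric message travels by MyChart while altruistic messages still travel by both routes. A message comparison pooled over contact method then contains part of the MyChart-email difference. The same happens to the contact comparison if message content matters.

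Section 8.1 leaves this path open. It does not say whether the unit dropped is a cell or a level, how many drops are allowed, or how the main effects are tested afterwards. One message could be reported as better only because its surviving invitations used the better route.

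**Working it through.** **The plan's own figure.** Five comparisons at 0.01 sum to 5 × 0.01 = 0.05; for independent tests, 1 − 0.99^5 = 0.0490. The stated total is right.

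**Assumed inputs.** The documents give no engagement rates or quarterly volumes. The checks assume no true message effect, equal allocation over active cells, a two-sided 0.01 test, email rates of 5% or 10%, MyChart rates of 5% to 15%, and either 5 quarters of 1,000 or 4,000 invitations or 8 quarters with 6,000 to 20,000 in total. One population is modelled, so these volumes apply to whichever of 3b or 3c is being tested.

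**Step 1: one cell dropped, by hand.** Email/ego-centric is dropped after quarter 1 of 5, with 1,000 invitations per quarter, email 5% and MyChart 8%.
- Each surviving cell: 250 + 4 × 1,000/3 = 1,583. Dropped cell: 250.
- Altruistic: (1,583 × 5% + 1,583 × 8%) / 3,167 = 6.50%.
- Ego-centric: (250 × 5% + 1,583 × 8%) / 1,833 = 7.59%.
- Overall rate 345/5,000 = 6.90%; SE = √[0.069 × 0.931 × (1/3,167 + 1/1,833)] = 0.74 points; expected z = 1.09/0.74 = 1.47.
- Chance of a significant result in that direction: about Φ(1.47 − 2.58) = 0.13 (0.138 from the power routine), against 0.005 expected per side. At 4,000 per quarter z doubles to about 2.93 and the chance is 0.64. For 5% v 10% the two figures are 0.38 and 0.97.

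**Step 2: a whole level dropped, by hand.** If email is dropped instead, each message has 250 email and 2,250 MyChart invitations. Both pool to (250 × 5% + 2,250 × 8%) / 2,500 = 7.70%, so the message contrast stays balanced.

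**Step 3: simulating the drop decision.** 3,000 runs per scenario over 5 quarters. At each look the lowest cell is dropped if it differs from the best at p<0.01. Message is then tested at nominal 0.01. Each pair gives 1,000 / 4,000 invitations per quarter.

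| Email v MyChart | One cell drop at most, pooled | Repeated cell drops, pooled | Whole level dropped, pooled |
|---|---|---|---|
| 5% v 5% | 0.010 / 0.013 | 0.010 / 0.009 | 0.015 / 0.017 |
| 5% v 6% | 0.008 / 0.014 | 0.009 / 0.010 | 0.012 / 0.011 |
| 5% v 8% | 0.036 / 0.498 | 0.018 / 0.031 | 0.012 / 0.007 |
| 5% v 10% | 0.225 / 0.963 | 0.022 / 0.084 | 0.011 / 0.009 |
| 10% v 15% | 0.084 / 0.801 | 0.018 / 0.046 | 0.011 / 0.008 |

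In both cell-drop columns, a Cochran-Mantel-Haenszel (CMH) test within contact method and quarter gave 0.008 to 0.015.

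**Step 4: eight quarters, 6,000 to 20,000 invitees.** With one cell drop at most, the pooled message test rejects in about 4% to 37% of runs (5% v 7.5%) and 39% to 99% (5% v 10%). With repeated drops it is about 2% to 5% in both cases.

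**The case against.** The strongest reply is that the text does not say cells. Section 8.1 names email, MyChart, ego-centric and altruistic, and four factor levels fit its count as well as four cells do. Section 4.1.1 uses the word for contact method. Under the level reading the message test is not inflated. This stands: that the plan drops cells is something a reader might infer, not something it states. Equally, the word cannot carry its section 4.1.1 meaning when there are four of them, so the cell reading is not excluded.

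Second, the confounding needs two things together, a cell drop and a test pooled over the other factor, and no sentence prescribes the pooled test. If a modality is a cell throughout, the two MyChart cells still give a clean message contrast. That is fair, but main-effect hypotheses with a plain binomial test make pooling the natural default.

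Third, a reader might take the large error rates as the expected result. The rule sets no limit on drops. If MyChart really is better, the second email cell usually goes too and later invitees are balanced again. The large rates need a one-drop limit that the documents do not contain.

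Fourth, it would be too strong to say that the plan has no stratified analysis. It promises one, with undefined strata. Nor can it be said that the recruitment result is biased. The Aim 3 analysis plan is not in the file. In the Aim 4 SAP the related section 8.2 rule became a single interim look and a robust Poisson model, with no consent arm dropped, so Aim 3 may also have been refined.

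**Conclusion.** The concern holds as a gap in specification with a conditional consequence. Section 8.1 leaves both the unit to be dropped and the post-drop test of Hypotheses 3a to 3c undefined, and one permitted reading gives a confounded main-effect test.

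Under the assumed rates and volumes, the message false-positive rate at nominal 1% is about 2% to 5% with repeated cell drops and contact rates of 5% v 7.5% to 10%. One five-quarter scenario (5% v 10%, 4,000 per quarter) reached 8.4%. Rates from about 4% to over 90% arise only if exactly one cell stays dropped. Inflation is not material if a whole level is dropped or if contact rates differ by 0 to 1 point. The condition that creates the problem for 3b and 3c, a real contact effect, is the trial's own Hypothesis 3a.

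This affects a secondary aim, and the documents do not show that any recruitment arm was dropped.

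**What to change.** In section 8.1:

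1. Define a modality as a factor level. Apply the drop rule only to a whole level: a contact method, or a message within its own population (obese or non-obese).
2. Replace the plain binomial test with a CMH test stratified by the other factor and by allocation period: 3b and 3c by contact method, 3a by message. Only concurrently randomised invitees are then compared. Stratifying by period also protects 3a after a contact method is dropped, when later invitees all use one route and any drift in response over time would otherwise enter the contrast.
3. If a cell has already been dropped, re-run the main-effect tests this way.

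The cost is protocol or SAP wording and a few lines of code; contact method, message and invitation date should already be on record. The downsides are that a single poor cell can no longer be dropped alone, and that invitations sent after a level is dropped add nothing to that factor's own contrast.

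The change removes the confounding, not the effect of repeated looks. With level drops and the CMH test, the five-quarter simulation gave 0.007 to 0.038 for message, because a message dropped at an interim look keeps its significant result. Those values lie within the 0.05 total for five tests at 0.01, but the number of looks still has to be fixed in advance.
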